### Statistical methods

Demographic and outcome data collected at baseline will be reported either as means with standard deviation or as frequencies with percentages according to their levels of measurement as a whole sample and by groups. Generalized estimating equations (GEE) will be employed to separately test the hypothesis on the five outcomes as dependent variables (i.e., mental well-being, depressive symptoms, loneliness, health-related quality of life, and perceived social support), The independent variables will be the same across all GEEs: the group (two categories: intervention and control groups), the timepoint (two categories: T0 and T1), and the interaction term (i.e., group × timepoint). The primary interpretation of the results will be based on the intention-to-treat analysis without adjusting for covariates [53, 54]. Sensitivity analysis will be conducted to compare the results of different analysis methods, including intention-to-treat, as-treated, and adherers-only analyses [55]. The level of significance will be set at 0.05. Missing data (e.g., due to dropout or death) will be managed following Jakobsen’s algorithm with multiple methods (e.g., multiple imputation) according to the missing pattern [56].

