#### Interventionists

The interventionists are trained young volunteers who are studying in a post-secondary institution (i.e., Tung Wah College). Tung Wah College requires students to attend community services for 40 h as a form of service learning, which is also a graduation requirement. Serving as a volunteer interventionist in this project will be counted as community service required by the college. The same volunteer will deliver the intervention to the same group of participants throughout the 6-week intervention period. A train-the-trainer program will be provided by the research team to the young volunteers. The program will provide standardized training to the volunteer interventionist on skills of delivering the intervention and establishing rapport with the participants (e.g., communication skills). The research officer will supervise each training session to ensure that the interventions are delivered identically across groups. The interventionists deliver the intervention in an interventionist-to-participant ratio of 1:3. To ensure good intervention fidelity, the young volunteers will be qualified to become interventionists in this program after they have completed a 2-h train-the-trainer program. The contents of the train-the-trainer cover the activities for operating the VR experience system, familiarizing with the standardized intervention implementation manual, as well as the essential communication skills with older people with physical disabilities. The research team will pay site visits to the research venue and observe the intervention by checking the implementation steps against the implementation manual. Regular research team meetings will be conducted to solve problems hindering the interventionists from following the intervention protocol.

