### Sample size

In the literature, there is a lack of randomized controlled trials evaluating the effect of therapeutic VR experience on mental well-being using specifically in older people with physical disabilities. A similar study evaluating the effects of feedback-based virtual reality exercise on mental health (measured by the mental component summary of the Short-Form Health Survey–36 items) in older women showed that the between-group effect size at the follow-up timepoint is moderate (i.e., *d*= 0.407) [49].

A priori power analysis using G*Power employing the statistical test of two-tailed *t*-test (means: difference between two independent means of two groups) is employed. We assume that The level of significance is set at 0.05. The effect size *d*is set at 0.407 [49]. The power is set at 0.8. The group allocation ratio is set at 1:1. It is estimated that 192 samples are needed with 96 samples in each group. Considering the attrition rate of 11.3% referring to another similar study examining the effects of a VR hands-on horticultural therapy on institutionalized older people [28], the total sample size of the proposed study is estimated to be 216.

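### The VR arm is treated in fixed groups of three, but the sample size assumes independent participants and the GEE as described makes no provision for the delivery group

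*Protocol article*

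**What the plan says.** **Delivery.** Under Allocation, participants are randomised individually. In the VR arm they are then treated in small fixed groups. The Interventionists section says "The interventionists deliver the intervention in an interventionist-to-participant ratio of 1:3" and "The same volunteer will deliver the intervention to the same group of participants throughout the 6-week intervention period". Table 1 and the accompanying text set 12 one-hour sessions, each with 30 minutes of group discussion after the VR exposure. The Groups section gives controls the usual care of the home and describes no trial delivery group for them.

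**Sample size.** The calculation is for a "two-tailed *t*-test (means: difference between two independent means of two groups) is employed". Its settings are "The level of significance is set at 0.05", "The effect size *d*is set at 0.407", power 0.8 and 1:1 allocation. The result is "It is estimated that 192 samples are needed with 96 samples in each group", raised to 216 for 11.3% attrition. No ICC or design effect appears.

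**Analysis.** Statistical methods lists the GEE predictors as "the group (two categories: intervention and control groups), the timepoint (two categories: T0 and T1), and the interaction term". The primary interpretation is by intention to treat and unadjusted for covariates, and "The level of significance will be set at 0.05". No cluster unit, working correlation or standard-error type is named, and neither the volunteer nor the delivery group is mentioned. The sensitivity analyses vary only who is analysed and in which arm.

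**The concern.** Three residents who share one volunteer and six hours of group discussion (12 × 30 minutes) over six weeks may drift in the same direction: a skilled volunteer or a congenial group lifts all three, and a poor one lifts none. The Background counts the single-player format of earlier VR as a weakness because it may not foster peer support, so shared influence is part of the rationale. Planning on exactly zero within-group correlation sits uneasily with that.

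This correlation arises after randomisation and only in the VR arm. If the GEE clusters on the participant, its robust standard error accounts for the two measurements on one person but not for correlation between the three people in a group. The standard error of the group-by-time term is then too small and the 5% level is exceeded. If the grouping is respected, the standard error is right but power falls below the planned figure, which has almost no reserve.

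**Working it through.** **Inputs from the protocol.** d = 0.407 with SD 1 on the standardised scale; two-sided alpha 0.05; 96 evaluable per arm; attrition 11.3%; delivery groups of m = 3 in the VR arm; no trial grouping in the control arm.

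**Assumption.** The within-group ICC is not given. Values from 0.01 to 0.20 are used.

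**Step 1: reproduce the plan.** The noncentrality is 0.407 × √(96/2) = 2.820 on 190 degrees of freedom. Power is 0.801 at 96 per arm and 0.797 at 95, so 192 is confirmed, with essentially no margin. For attrition, 192 / 0.887 = 216.5, which the protocol gives as 216.

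**Step 2: add the grouping in the VR arm only.**
- VR-arm design effect: DE = 1 + (m − 1) × ICC = 1 + 2 × ICC. Control arm: 1.
- Variance inflation of the difference with equal arms: VIF = (DE + 1) / 2 = 1 + ICC.
- True alpha if the grouping is ignored: 2 × [1 − Φ(1.96 / √VIF)].
- Power if it is respected: noncentral t with noncentrality 2.820 / √VIF.

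Example at ICC 0.10: DE = 1.20, VIF = 1.10, √VIF = 1.049. Alpha = 2 × [1 − Φ(1.869)] = 0.062. The noncentrality is 2.820 / 1.049 = 2.689, and power is 0.763.

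| ICC (assumed) | DE, VR arm | SE multiplier | True alpha, grouping ignored | Power, grouping respected |
|---|---|---|---|---|
| 0 | 1.00 | 1.000 | 5.0% | 0.801 |
| 0.01 | 1.02 | 1.005 | 5.1% | 0.797 |
| 0.02 | 1.04 | 1.010 | 5.2% | 0.793 |
| 0.05 | 1.10 | 1.025 | 5.6% | 0.782 |
| 0.10 | 1.20 | 1.049 | 6.2% | 0.763 |
| 0.20 | 1.40 | 1.095 | 7.4% | 0.726 |

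**Step 3: check on the planned contrast.** With complete data, the group-by-time term is the difference in mean change. It was simulated 40,000 times per setting with participant-level robust standard errors and an assumed T0–T1 correlation of 0.5. True alpha was 5.8 / 6.5 / 7.8% at ICC 0.05 / 0.10 / 0.20, against 5.15% at ICC zero. Standard errors computed from group means brought alpha back to about 5.3–5.4%, with power 0.786 / 0.768 / 0.729. These agree with the table to within about half a percentage point.

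**The case against.** **The GEE text does not show that the grouping is ignored.** This stands. The quoted list gives mean-model terms, whereas clustering in a GEE is set by the cluster identifier. A GEE clustered on the delivery group, with each control as a singleton, would have exactly these terms, and a separate analysis plan may specify one. A reader might infer that the protocol treats all participants as independent throughout. That is explicit only for the sample size; for the GEE it is a reasonable inference from the repeated timepoint factor and the absence of any mention of the group.

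**The ICC is unknown and the groups are small.** This also stands. A reader might conclude that the 0.05 level and 0.80 power simply fail. At ICC 0.01–0.02 alpha is 5.1–5.2% and power about 0.79–0.80, which matters little. Attrition shrinks the groups as well: with independent dropout of 11.3% each member keeps on average 2 × 0.887 = 1.77 co-members, an effective size of about 2.8. At ICC 0.10 that gives alpha about 6.0% and power 0.767.

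**The power of the planned test is not fixed by the t-test.** Correct. The group-by-time term also depends on the T0–T1 correlation, which is not given. The change-score variance is 2(1 − ρ) times the single-timepoint variance, so the t-test basis corresponds to ρ = 0.5. At ρ = 0.6, power respecting the groups is 0.86 / 0.84 / 0.80 for ICC 0.05 / 0.10 / 0.20; at ρ = 0.4 it is 0.73 even with no clustering. The power figures above therefore correct the protocol's own statement on its own basis and do not predict the power of the GEE. Alpha inflation remains at any ρ: at ICC 0.10 the simulation gave 6.1%, 6.5% and 7.2% for ρ = 0.3, 0.5 and 0.7.

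**A volunteer could lead two groups.** With six residents per volunteer correlated alike, ICC 0.05 / 0.10 / 0.20 would give alpha 6.5 / 8.0 / 11.0% and power 0.75 / 0.71 / 0.63. The 40-hour service requirement leaves room for this, but the protocol neither states nor excludes it, so these figures should carry no weight in the main conclusion.

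**Conclusion.** The point holds in conditional form. Fixed groups of three in one arm are documented, and the sample size explicitly assumes independence. The GEE as described makes no provision for the delivery group. If its clusters are participants, any positive ICC understates the VR-arm variance. Over assumed ICCs of 0.01 to 0.20, alpha runs from about 5.1% to 7.4% if the grouping is ignored, and power from about 0.80 down to 0.73 if it is respected. The consequence is modest at low ICC, material from about 0.10, and larger only if volunteers lead more than one group.

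This rests on the assumed ICC, full groups of three, 96 evaluable per arm, no correlation introduced by the trial among controls, and the protocol's t-test basis. Randomisation is individual, so the comparison itself is not invalidated; what needs correction is the standard error and the power statement. Severity: should fix.

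**What to change.** 1. Record a volunteer ID and a delivery-group ID for every VR participant from the first session. The article places recruitment in the future, so this can be done prospectively. The protocol does not say that this link is recorded, and without it no later analysis can allow for the grouping.
2. Name the GEE cluster: the delivery group in the VR arm (the volunteer, if one leads several groups) and each participant as a singleton in the control arm. Keep both timepoints of a person in the same cluster and use a small-sample-corrected robust standard error, since 108 / 3 = 36 VR clusters is not many. A partially nested mixed model is an equivalent choice. The listed model terms need not change.
3. Keep N = 216 and replace the single 0.80 with a range over stated ICC assumptions: about 0.76–0.80 for ICC 0.01–0.10 with groups of three.
4. State whether a volunteer may lead more than one group.

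The cost is one or two ID fields, a few lines of analysis text and a slightly less favourable power statement, with no extra participants. If the sponsor would rather restore 0.80 on the t-test basis, 96 × 1.05 gives 101 per arm, or 202 / 0.887 = 228 in total, at ICC 0.05. At ICC 0.10, 96 × 1.10 gives 106 per arm, or 212 / 0.887 = 240 rounded up.

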### Outcomes

Demographic data including age, gender, level of education, number of chronic illnesses, length of stay in the LTCF, and experience of participation in VR activities will be collected. Demographic data will be collected at T0 (i.e., baseline, week 0) only. The primary outcome is mental well-being. The four secondary outcomes are depressive symptoms, loneliness, health-related quality of life, and perceived social support. All outcome data will be collected at T0 (i.e., baseline, week 0) and T1 (i.e., the week immediately after the completion of the intervention, week 7).

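### The sample size assumes a follow-up-only t-test but the primary GEE tests change, so power reaches 0.80 only if the T0–T1 correlation is about 0.5 or higher; adjusting for T0 would remove that condition

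*Protocol article*

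**What the plan says.** **Sizing (Protocol article, Sample size).** The calculation is for a "two-tailed *t*-test (means: difference between two independent means of two groups) is employed". Its inputs are: "The effect size *d*is set at 0.407", "The power is set at 0.8" and "The level of significance is set at 0.05". The effect size comes from a study of virtual reality exercise in older women, of which the article says that "the between-group effect size at the follow-up timepoint is moderate". The result is 96 per arm, 192 in total, raised to 216 for 11.3% attrition. This section mentions neither the GEE nor a correlation between the two assessments.

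**Analysis (Protocol article, Statistical methods).** Each of the five outcomes is the dependent variable of a GEE with three terms: group, timepoint (T0 or T1) and group × timepoint. On adjustment it says: "The primary interpretation of the results will be based on the intention-to-treat analysis without adjusting for covariates". T0 therefore enters as a repeated response and not as a covariate. The section does not name the decisive coefficient, but in this model the interaction is the term that carries the group difference in change.

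**Data (Protocol article, Outcomes).** "All outcome data will be collected at T0 (i.e., baseline, week 0) and T1", so the baseline score is scheduled for every participant.

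**The concern.** The stated power belongs to a comparison of T1 means, while the planned primary test compares changes from T0 to T1. These two contrasts estimate the same effect under randomisation, but their precision differs by a factor that depends on the T0–T1 correlation. Without a stated correlation, the 0.80 does not carry over to the planned test.

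The model also estimates a group difference at T0, which randomisation makes zero in expectation. Estimating it costs precision that a baseline-adjusted model would keep. At stake are the power on the primary outcome, WHO-5, and the precision of all five treatment estimates.

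**Working it through.** **Inputs.** From Sample size: d = 0.407, two-sided alpha 0.05, 96 per arm, 1:1. From Statistical methods: group, timepoint and group × timepoint, unadjusted. Assumed here, because the article gives none: rho, the T0–T1 correlation, shown from 0.2 to 0.8. Also assumed: equal SDs at T0 and T1, d in units of the follow-up SD, complete data on 96 per arm, and no clustering by facility or volunteer group.

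**1. The plan's own figure.** For the follow-up t-test, the noncentrality is 0.407 × √(96/2) = 2.82 with 190 df, and power is 0.801. The smallest n reaching 0.80 is 96 per arm, as stated. For attrition, 192/0.887 = 216.5, against the stated 216. The sizing arithmetic is therefore sound for the test it names.

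**2. What the planned model tests.** With two groups, two timepoints and all three terms, the model is saturated in the four means. The interaction equals (mean T1 − mean T0 in intervention) − (mean T1 − mean T0 in control). On simulated complete data, GEE fits with independence and with exchangeable working correlation both gave the same estimate and robust standard error as the difference in mean change.

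**3. Variances relative to the follow-up-only contrast (equal SDs).**
- Change contrast: 2(1 − rho)
- Baseline-adjusted contrast: 1 − rho²
- Ratio of change to adjusted: 2(1 − rho)/(1 − rho²) = 2/(1 + rho), which exceeds 1 for every rho below 1

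The change contrast matches the follow-up t-test where 2(1 − rho) = 1, that is, at rho = 0.5. If the SDs differ, the break-even is SD(T0)/(2 × SD(T1)): 0.4 for a T0-to-T1 SD ratio of 0.8, and 0.6 for a ratio of 1.2.

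**4. Power at 96 per arm.** Divide d by the square root of the variance factor and use the noncentral t with 190 df. At rho = 0.3, for example, the change contrast has 0.407/√1.4 = 0.344 and power 0.66; the adjusted contrast has 0.407/√0.91 = 0.427 and power 0.84.

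| rho | Power, planned change contrast | Power, baseline-adjusted | n per arm for 0.80, change | n per arm for 0.80, adjusted | Variance ratio 2/(1 + rho) |
|---|---|---|---|---|---|
| 0.2 | 0.60 | 0.82 | 153 | 92 | 1.67 |
| 0.3 | 0.66 | 0.84 | 134 | 88 | 1.54 |
| 0.4 | 0.73 | 0.87 | 115 | 81 | 1.43 |
| 0.5 | 0.80 | 0.90 | 96 | 73 | 1.33 |
| 0.6 | 0.88 | 0.94 | 77 | 62 | 1.25 |
| 0.7 | 0.95 | 0.98 | 58 | 50 | 1.18 |
| 0.8 | 0.99 | 0.997 | 39 | 36 | 1.11 |

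At rho = 0 the adjusted analysis has the same variance as the follow-up t-test, with power about 0.80. That is its floor.

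**5. The gain as sample size.** Relative to the change contrast, adjustment needs a fraction (1 − rho)/2 fewer participants for equal precision: 35%, 25% and 15% at rho 0.3, 0.5 and 0.7. Relative to the follow-up t-test behind the planned 192, the saving is rho²: 9%, 25% and 49%. The two comparators give opposite trends, so the comparator must be named whenever a saving is quoted.

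**The case against.** The strongest case against is that nothing here is wrong, only less than optimal. The unadjusted group × timepoint GEE is a common, valid model, and the article cites support for its unadjusted intention-to-treat analysis. Above rho = 0.5 the follow-up t-test is a conservative basis for sizing it. The article reports reliability figures on the high side for three secondary scales: test–retest 0.76 for PHQ-9, 0.65 for MSPSS and 0.7–1.0 for EQ-5D-5L. Rho of 0.65 would give the planned contrast power 0.92, and 0.76 would give 0.98. A condensed article may also leave the working correlation and the decisive contrast to a fuller document.

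Much of this stands, and it rules out four stronger readings that a reader might infer:

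- *Power is 0.80 only near rho = 0.5.* No: 0.5 is a lower threshold, and power exceeds 0.80 above it.
- *The trial is underpowered.* Not shown. The article gives no rho and nothing that places it below 0.5.
- *The planned estimate is biased by regression to the mean.* Not over randomisation. Regression to the mean matters only conditional on a chance imbalance at T0.
- *The baseline score is wasted.* No: above rho = 0.5 the change contrast beats the follow-up-only test.

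The objection does not remove the point itself. The reliability figures are not seven-week correlations, and none is given for WHO-5, so they do not settle rho for the primary outcome. The model terms and the absence of adjustment are stated in the article, not left open. The loss of precision against baseline adjustment holds at every rho below 1, although at 0.8 it is small in power terms (0.993 against 0.997).

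**Conclusion.** The point holds as one of alignment and efficiency. The sizing test and the planned primary contrast have different variances, and no correlation is stated to link them. The planned contrast has at least 0.80 power only if rho is about 0.5 or higher. At rho = 0.3 it would have 0.66 and would need 134 evaluable per arm rather than 96. It has 1.54, 1.33 and 1.18 times the variance of a baseline-adjusted analysis at rho 0.3, 0.5 and 0.7.

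It is neither an arithmetic error nor a threat to validity. The figures rest on the assumptions listed with the inputs and on reading the interaction as the test of effect. The threshold of 0.5 moves if the SDs at T0 and T1 differ. The case for changing the model does not depend on knowing rho, because adjustment is more precise than the change contrast at every rho below 1 and keeps power at about 0.80 or above throughout.

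**What to change.** Make the primary model for all five outcomes baseline-adjusted, in one of two ways:

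- regress the T1 score on group and T0 score; or
- keep the GEE but drop the group main effect, so that both arms share a T0 mean, and use an exchangeable or unstructured working correlation. An independence structure would reduce this model to the follow-up-only comparison and lose the gain.

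Amend the sentence on covariates so that it allows T0 adjustment in the primary analysis. Keep the unadjusted group × timepoint GEE as a sensitivity analysis. In Sample size, state the power for the model actually used, with the assumed T0–T1 correlation and a range around it.

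The cost is analysis wording only. T0 is already scheduled for everyone, and the planned 192 evaluable participants need not change. According to Trial status, recruitment had not begun, so at that stage the change could be specified before any data were seen.

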Adverse effects commonly reported on older people after using virtual reality-based interventions include cybersickness, fall injuries, dizziness, and eyestrain, although the incidence is low [57]. To ensure safety, all participants will attend the intervention in a sitting position to minimize the risk of falls. To minimize the risk of cybersickness, dizziness, and eyestrain, the VR experience in each section is limited to 20 min only. After the completion of the intervention, the interventionist will stay with the participants for 15 min more and examine the participants for any common adverse effects or discomforts. Basic training will also be provided to the interventionists to identify common adverse effects (e.g., signs of cybersickness) and provide immediate management for mild symptoms (e.g., lying the participants flat on the bed with eyes closed for a few minutes to prevent fall injuries). The LTCF staff members will be trained to observe common adverse effects on the participants. All suspected adverse effects will be recorded in a logbook. The interventionists and LTCF staff members will inform the trial steering committee when suspected adverse effects are observed. If the adverse effects are severe (e.g., fall injuries), participants will be immediately sent to a hospital for immediate treatment. If the adverse effect is severe, the case of suspected adverse effects will also be discussed in the advisory panel to determine whether it is related to the intervention. The project implementation team will meet the participants and the staff members of the collaborative LTCF regularly. If suspected adverse events related to the interventions are reported by the participants, interventionists, or LTCF staff members, the implementation team will report them to the trial steering team. Judged by the trial steering team, if the events are likely to be related to the intervention, the advisory panel will be informed and the panel will decide if the adverse events are related to the trial. Subsequently, the advisory panel will decide to either continue the trial, withdraw the affected participants from the trial, revise the trial protocol, or terminate the trial. An independent audit company will be hired to audit the trial and provide an audit report once per year.

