### Eligibility criteria

#### Inclusion

Aged 60 years or above;LTCF residents; andPhysical disabilities, as defined by the modified Barthel Index (MBI) score of ≤ 90 (i.e., moderately dependent or worse) [38].

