#### Groups

Participants allocated to the intervention group will participate in the 6-week VR experience program. Participants allocated to the control will receive the usual care provided by the LTCF, such as personal care, regular basic medical and nursing care, and social support activities, as committed by the Social Welfare Department [37].

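### Only VR participants get a structured check for harms, and reporting is filtered by suspected cause, so no equal count of falls and dizziness in the control arm is assured

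*Protocol article*

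**What the plan says.** All of this is in the Protocol article.

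- **Detection (Monitoring).** The named risks are cybersickness, fall injuries, dizziness and eyestrain. Once the intervention is finished, "the interventionist will stay with the participants for 15 min more and examine the participants for any common adverse effects or discomforts". Two further channels are given: "The LTCF staff members will be trained to observe common adverse effects on the participants", and "The project implementation team will meet the participants and the staff members of the collaborative LTCF regularly".
- **Recording (Monitoring).** The logbook is for suspected adverse effects. Interventionists and facility staff tell the steering committee when they see one.
- **Escalation (Monitoring).** The implementation team reports to the steering team "If suspected adverse events related to the interventions are reported by the participants, interventionists, or LTCF staff members". The steering team then considers whether a link is likely, and if so the advisory panel is told. Severe suspected effects have their own route, in which the panel itself discusses relatedness. The panel decides whether the trial goes on, is revised or ends. It also receives a three-monthly report that covers suspicion of adverse effects.
- **Control arm (Groups).** "Participants allocated to the control will receive the usual care provided by the LTCF".
- **Population (Inclusion).** Residents are aged 60 or over and have a "modified Barthel Index (MBI) score of ≤ 90 (i.e., moderately dependent or worse").
- **Outcomes.** Besides mental well-being, "The four secondary outcomes are depressive symptoms, loneliness, health-related quality of life, and perceived social support". Table 2 schedules these five and the demographic data, and Statistical methods analyses these five.

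**The concern.** Fall injuries and dizziness are on the plan's own list of risks, and both plausibly occur without VR in residents this dependent. The way to separate a VR effect from background is to compare the randomised arms on events collected in the same way. The process as written looks harder for events in one arm. It then asks whether VR is suspected before an event is recorded or passed on.

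Two things are at stake. The advisory panel must judge relatedness and decide on continuation, and without an assured comparator it could dismiss a raised fall rate as background or blame background falls on VR. Later, according to the Discussion, the program is to be offered for free download to other facilities, whose staff would want to know its harms relative to usual care.

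An analysis plan could not repair this afterwards, because control-arm events that were not recorded at the time are hard to reconstruct.

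**Working it through.** **Step 1. The channels side by side.**

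| Channel | Reaches the control arm? | Needs prior suspicion? |
|---|---|---|
| 15-minute examination by the interventionist | No: controls have no session and no interventionist | No |
| Observation by trained facility staff | Not stated | Yes: what is logged is a suspected effect |
| Regular meetings with participants and staff | Not stated | Yes: the report that follows concerns events suspected to be related |
| Severe cases to the panel | Not stated | Yes: it starts from a suspected effect, though relatedness is decided at the panel |
| Non-severe cases to the panel | Not stated | Yes, twice: suspicion first, then the steering team's view that a link is likely |

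The table shows no channel that covers both arms in the same way and is free of a judgement about cause.

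**Step 2. Inequality of the examination.** Two sessions per week × 6 weeks = 12 sessions. If the examination follows each session, a VR resident can be examined up to 12 times. If it happens once at the end of the course, which the wording also allows, the number is 1. For a control resident it is 0 on either reading.

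**Step 3. Arm size.** The plan's own figure is reproduced first. With d = 0.407, two-sided alpha 0.05 and power 0.80, the t-test calculation gives 95.73, so 96 per arm and 192 in total. Allowing for 11.3% attrition, 192 / (1 − 0.113) = 216.46, which the plan gives as 216. At 1:1 this is 108 per arm. The calculation is sound and serves here only to set the denominator.

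**Step 4. Background events expected (assumed rates).** The article gives no background rate. Let p be the share of residents with a fall, dizziness or hospital transfer between allocation and the T1 week, with no VR effect. Expected residents affected per arm = 108p; chance of at least one in the VR arm = 1 − (1 − p)^108.

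| p (assumed) | Expected per arm | Chance of at least one |
|---|---|---|
| 2% | 108 × 0.02 = 2.2 | 89% |
| 5% | 108 × 0.05 = 5.4 | 99.6% |
| 10% | 108 × 0.10 = 10.8 | over 99.9% |

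Even at the low end, the panel should expect some background events among VR residents.

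**Step 5. What a full count could show.** With 108 per arm and a two-sided 5% test of two proportions (normal approximation), power to detect a doubling is 0.136 from 2%, 0.285 from 5% and 0.539 from 10%. Power to detect a tripling is 0.322, 0.69 and 0.962. Observed counts of 5 and 0 would give a two-sided Fisher p of 2 × (108·107·106·105·104) / (216·215·214·213·212) = 0.06. An equal count would therefore give an unfiltered estimate with a confidence interval, not a firm test for rare events.

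**The case against.** The strongest reply is that the text is more open than it looks. Facility staff observe participants, and the implementation team meets participants and staff; neither is limited to one arm or to session days. Elsewhere in the article the word participants covers both groups. The sentence on related events governs escalation, while recording in the logbook is a separate step. For severe cases, with fall injuries as the article's own example, relatedness is settled at the panel and not before it. Death is named under Statistical methods as a cause of missing data, so deaths would probably be noticed in either arm. A check for headset symptoms after VR is reasonable in itself, and safety tables are commonly left to a fuller document.

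Much of this stands. A reader might infer that harms are sought only after VR, that control-arm events are never recorded, or that the panel will see one arm alone. The article does not say so, and nothing in it bars logging a control resident's fall. The absence of a safety table from a journal article is not the fault either.

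What the reply does not remove is the suspicion built into each stated step. Staff log suspected effects, and the severe route also starts from one. The same section states that "all participants will attend the intervention in a sitting position to minimize the risk of falls", which suggests that its participants are VR attendees. For non-severe events, the likelihood of a link is judged by the steering team, which includes the sponsor, before the panel, described as independent of the sponsor, is informed. Staff also know the allocation, since Blinding forbids them to disclose it to the assessors, so suspicion can follow the group label.

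**Conclusion.** The point holds in this form: the structured examination is tied to VR exposure, recording and escalation depend on suspected cause, and no channel assures an equal count in the control arm. Falls and dizziness in VR residents therefore cannot be reliably separated from background by randomised comparison. The documents do not support the stronger conclusions that control events will certainly go uncounted or that no comparison by arm will be possible.

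The size can only be illustrated. Under an assumed 2% to 10% background, about 2 to 11 residents per arm would have such an event with no VR effect. The conclusion rests on that range only for scale. It otherwise rests on the harms steps as written and on the premise that falls and dizziness occur without VR in residents who are moderately dependent or worse. The efficacy analysis and the sample size are unaffected. The change should be made before enrolment, because missed events are hard to recover; at the time of the article recruitment had not begun.

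**What to change.** For all randomised participants in both arms, have the facility staff log every fall, fall injury, dizziness episode, hospital transfer and death, with its date, from allocation to the T1 week and regardless of suspected cause. Judge relatedness after recording. Report counts by randomised arm to the advisory panel and in the results. Keep the 15-minute check as a separate tolerability record for the VR arm only, and do not add its findings to the between-arm counts. Keep the log away from the outcome assessors so that it does not reveal allocation.

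The cost is small. Staff training and a logbook are already planned, so the additions are somewhat more recording for control residents and one safety table, with no new staff or visits. One limitation remains: facility staff know the allocation, so the comparison is most reliable for objective events (falls, transfers, deaths) and weaker for dizziness. The report should say so.
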